## Abstract

**Background:**

Rumination is a transdiagnostic process present in several psychological disorders, involving repetitive negative thinking that individuals may perceive as difficult to control. While the roles of numerous mechanisms underlying rumination have been supported, experiential avoidance (EA) still lacks empirical backing, despite a strong theoretical foundation, partly due to difficulties in examining EA in an ecologically valid context. One promising approach to addressing this challenge is through reducing EA using mobile health (mHealth) and ecological momentary intervention (EMI), and assessing any subsequent decrease in rumination’s deleterious outcomes.

**Objective:**

This paper outlines the protocol for a randomized controlled trial using a novel mHealth EMI to address EA in the context of rumination. The app was developed by a multidisciplinary team, incorporating feedback from potential end users.

**Methods:**

Consenting individuals (target N=60) who meet the inclusion criteria (self-reporting problems with repetitive negative thinking) will be randomly assigned to 1 of 4 conditions: (1) intervention with therapist support and daily sampling, (2) intervention without support and with daily sampling, (3) partial intervention (emotion validation EMI only) with daily sampling, or (4) control (daily sampling only). The intervention consists of a series of modules delivered over 4 weeks, with assessments conducted before and after intervention, and again at 1-month follow-up (plus an additional 3-month follow-up for intervention participants). Data will be collected both through online self-report assessments and via the app itself. The potential of the EMI to modify the maladaptive feature of repetitive negative thinking will be assessed using mixed-design ANOVA, while the links between avoidance-mood and rumination-mood, in terms of the moderating effect of trial condition, will be evaluated using multilevel models. These will be assessed as primary outcomes. Secondary outcomes are the effects of a supporting therapist on postintervention outcomes in the intervention groups, and time spent using the app as a measure of engagement (analyzed using the mixed-design analysis of covariance). Compliance will be defined as completing both of the first 2 weeks of intervention content in full, and 5 out of the 6 exercises from weeks 3 and 4. Additionally, the study will control for both the amount of time spent in the app and the length of responses to open-ended questions.

**Results:**

Recruitment and enrollment for the trial are expected to begin in May 2025 and be completed by July 2025. Data collection will conclude once the target sample size for each of the 4 conditions has been reached. The main results of the trial are expected to be submitted for publication in October 2025.

**Conclusions:**

The outcomes of this research trial will not only provide insights into the clinical capabilities of the app, including its usability and acceptability in real-world contexts (and its potential future viability as a scalable product), but will also offer valuable theoretical insights into the role of EA in maladaptive rumination.

**Trial Registration:**

ClinicalTrials.gov NCT06570694; https://clinicaltrials.gov/ct2/show/NCT06570694

**International Registered Report Identifier (IRRID):**

PRR1-10.2196/66067

## Introduction

### Rumination and Psychopathological Outcomes

Epidemiological data suggest that comorbidity is the rule rather than the exception [1], with it frequently observed in at least half of the diagnosed population [2]. The experience of comorbidity has significant negative implications for clinical severity and prognosis [3,4]. Additionally, the persistently moderate outcomes of treatment programs and high levels of posttreatment relapse indicate a still limited understanding of the mechanisms that initiate, underpin, and maintain a number of psychiatric disorders [5].

Transdiagnostic models represent a shift away from disorder-centric approaches to the understanding and treatment of psychological disorders. Instead of focusing on a specific nosological diagnosis, they suggest focusing on processes that may serve as risk, maintenance, and relapse factors across multiple psychological disorders, thereby more effectively addressing the frequent comorbidity observed in mental disorders. Interventions based on transdiagnostic approaches have demonstrated positive outcomes in reducing symptom presentation across several disorders [3,6-10].

Rumination is a transdiagnostic process present in several psychological disorders [11]. Traditionally, rumination was explored in the context of mood disorders and defined as a mode of responding to distress that involves repetitively and passively focusing on symptoms of distress and the possible causes and consequences of these symptoms. Nevertheless, rumination is now recognized as being involved in numerous psychological disorders and adopts a broader definition—a form of repetitive thinking about 1 or more concerns perceived to be difficult to control [12]. While rumination may not necessarily be wholly maladaptive, it can become so when overgeneralized and used inflexibly [13], in which case it has been shown to impair emotional regulation and increase negative affect [14]. Thus, one can expect that addressing this maladaptive transdiagnostic process will result in a reduction of psychopathology symptoms (eg, [11]). Experimental studies that induce rumination in distressing contexts demonstrate elevated depressed and anxious mood [15]. Similarly, self-report studies find rumination to be a risk factor in numerous issues, including as a risk factor and consequence of depressive symptoms [16]; the onset, number, and duration of major depressive episodes [17-19]; and the development of generalized anxiety [19], social anxiety [19], eating disorders [19], posttraumatic stress [20], and borderline symptoms [21]. In addition to its symptomatological impact, rumination has also been shown to reduce the efficacy of psychological interventions [12].

Currently, several models explain the maladaptive nature of rumination—these involve abstract processing and dysregulation at the goal/action identification level (ie, adapting a specific processing mode to current requirements [22]); impairments in executive or attentional functioning [23,24]; or rumination as a learned, habitual response [13,23,24]. A recent H_Ex_A_Go_N model of rumination attempts to integrate the most prevalent theories with a relatively strong empirical background on the mechanisms maintaining maladaptive rumination, identifying rumination as a *h*abit, *ex*ecutive function impairment, *a*bstract processing mode, *go*al discrepancies triggering rumination, and the *n*egative valence of rumination content [12]. Thus, the authors suggest that rumination becomes a maladaptive, transdiagnostic process when it is used as a habitual, overgeneralized response to negative affect [12,25].

Nevertheless, the literature suggests that another mechanism could be involved in making rumination maladaptive and in reinforcing it as a habitual response—namely, experiential avoidance (EA). Although this mechanism features prominently in the theory of repetitive negative thinking (RNT), it has received very limited empirical support. This is not necessarily due to a lack of supportive data (eg, [25]), but rather to the small number of studies testing this hypothesis, largely because of the challenges involved in evaluating EA in empirical research.

### Mechanisms Underpinning Rumination: Examining the Role of Experiential Avoidance

EA refers to attempts to eschew emotional distress by engaging in maladaptive behaviors that temporarily allow escape from negative emotional experiences. Through the use of EA, individuals may disconnect from unpleasant emotions by altering the form or frequency of these experiences [26], even when such avoidance causes behavioral harm by interfering with goal pursuit and impairing learning through experience. This often leads to the adoption of additional maladaptive coping strategies, such as substance use [27].

Engagement in EA has adverse effects on the development, maintenance, and modification of chronic psychological disorders such as depression, due to its tendency to generate negative mood and initiate a maladaptive cycle of emotional distress and avoidance [28]. Consequently, EA may represent a core vulnerability for emotional distress [29]. To this end, randomized controlled trials delivering therapeutic interventions focused on reducing EA (such as acceptance and commitment therapy) have found that decreases in EA are associated with reductions in depressive and anxious symptoms [28,30,31].

As a mechanism underpinning rumination, however, despite some empirical evidence emerging to examine its role [12,32], EA continues to lag in terms of supporting data. This is despite the theoretical basis for the role of EA in rumination [22,33], where rumination serves as a means to avoid increased arousal and distress through an overgeneral, abstract style of thinking, despite its maladaptive implications for real-world problem-solving and long-term deleterious consequences for emotion regulation [22,24,25]. Of note, a study examining multiple indices of avoidance reported differential outcomes across the 3 modes of investigation (self-report, dichotic listening tasks, and psychophysiological measures), lending only partial support to the avoidance conceptualization of rumination [34].

Difficulties in examining the role of EA may, in part, be due to several methodological challenges associated with assessing EA in ecologically valid contexts. While experimental studies appear to lend support to an EA conceptualization of rumination [29,35], the tasks used to evaluate it in laboratory settings (eg, approach-avoidance task or dichotic listening task) do not reflect the real-world occurrences of EA. Similarly, while self-report evaluations connect EA with rumination [34,36], such data rely heavily on retrospective recollection, assuming that participants were aware of their use of (and the extent of their use of) avoidance. One alternative approach to examining the role of EA may involve adopting the experimental method, that is, reducing EA through ecological momentary intervention (EMI) [37], and examining any resulting reduction in the deleterious outcomes of rumination.

### Mobile Health as a Vehicle for Ecological Momentary Intervention

The availability of mental health services has struggled to keep pace with the growing demand for treatment [38,39]. One means of addressing this imbalance has been through the use of digital interventions, which offer the potential to provide accessible, rapid, and scalable pathways to intervention [40].

Mobile health (mHealth) apps represent a dimension of digital health provision and allow for the delivery of validated psychological interventions on-demand via smartphones. Because of the ubiquity of smartphones [41] and the opportunities afforded for personalization of provision, mHealth apps offer the potential to deliver rapidly scalable interventions that can expand the reach of mental health services while overcoming a number of barriers faced by traditional forms of treatment [42].

EMI further represents an opportunity to utilize ubiquitous devices, such as smartphones, to integrate treatment protocols into people’s everyday lives. Treatment can be delivered in natural environments as either a standalone intervention or as an addendum to existing treatment [43], and can be based on the outcomes of real-time daily sampling assessments also conducted in the real world (ecological momentary assessment [EMA]). The use of real-time assessment data allows for provision to be personalized and tailored to the general requirements of an individual client and, on a micro-level, as a form of opportune intervention within a specific environmental context [44]. As an assessment tool, EMA also helps overcome the limitations of global self-report measures, where retrospective recollections of emotions and events may be distorted by subsequent use of regulation strategies [45].

Literature has begun to explore the capabilities of mHealth EMIs as tools for mental health intervention, with promising results emerging across a range of conditions [46,47]. In addition to their potential therapeutic benefits, EMIs represent several methodological opportunities to improve ecological validity. First, the use of ubiquitous devices such as smartphones allows research to be conducted in real-world settings, reducing the reliance on laboratory-based experimental studies, where outcomes may, in part, be a product of the artificiality of the environment. Instead, the real-world nature of treatment delivery allows for the examination of intervention effects (eg, in the context of transdiagnostic processes) in real-world contexts. Second, while EMAs may not always be conducted in “real time” (eg, at the moment of symptom experience), data can be collected within a short period thereafter. The implementation of regular EMA also reduces the reliance of treatment efficacy studies on postintervention self-report data, which can be vulnerable to retrospective bias, particularly for individuals experiencing depressive disorders [48,49].

Uptake and engagement with mHealth, however, may be negatively associated with poor app design, technical issues, digital literacy, poor suitability of content, lack of professional support, and pathological factors (eg, low motivation), when content is delivered in a manner unsuited to user requirements, or when engagement is considered by users to be too labor intensive [50-55]. Numerous factors at both the individual and group levels have been identified that may affect the intention to use or uptake of digital interventions [56,57]. Effective multidisciplinary collaboration in app development, which acknowledges the intricate needs of target end users and incorporates these into the design of the intervention, is essential for improving acceptability, usability, and accessibility [58], particularly when interventions are deployed in unsupervised settings [59]. EMIs require unique considerations in their design, deployment, and evaluation [60], which help specify the procedures for collecting and examining user data and the circumstances under which the intervention may be delivered. Where EMIs actively respond to user data in real time, processes for determining appropriate intervention (while respecting user privacy) must also be considered.

### Study Objectives

The scientific verification of processes that underpin several transdiagnostic maladaptive cognitive processes and psychopathological outcomes has several benefits. First, successfully identifying such processes advances the theoretical understanding of transdiagnostic processes themselves and their contributing roles in psychopathology. Second, it has the potential to improve several psychological treatment programs by identifying valuable targets for intervention [21], which is particularly valuable in treating cases of comorbidity. Using EMI and EMA in clinical trials offers a unique opportunity to evaluate the mechanisms underlying transdiagnostic processes that are difficult to assess through traditional self-report or laboratory methods (eg, avoidance). This study aims to examine whether the avoidance-focused EMI for rumination can modify the maladaptive feature of RNT, as understood through the link between daily RNT and well-being, depressive, and anxiety symptoms, compared with an active control group. We anticipate that the link between daily rumination and its maladaptive outcomes (lower well-being and higher depressive and anxiety symptoms) will be weaker in the intervention groups compared with the control group. Additionally, the study aims to confirm the role of avoidance in RNT.

Furthermore, by splitting the intervention condition into 2 groups (1 receiving concurrent therapist support and 1 not receiving concurrent therapist support), the study aims to evaluate whether intervention outcomes may be enhanced by the added availability of a supporting therapist [61].

Finally, the study aims to examine whether the impact of the avoidance-focused EMI for rumination on depressive and anxious symptoms can, compared with an active control group, be mediated by changes in beliefs about emotion (valuation of negative emotions) [62]. Similarly, the study aims to assess the EMI in terms of similar mediation effects of beliefs about rumination [63].

## Methods

### Study Design

The study takes the form of a 4-arm, parallel-group randomized controlled trial. Total study participation will last approximately 2 months, including preintervention eligibility screening, a 4-week intervention period using the app content and daily sampling, postintervention assessments at the end of the intervention, and a 1-month follow-up period (during which the app will remain available for self-directed use without daily sampling), concluding with follow-up assessments and measurement of any engagement with the app during this period. At this point, control participants will receive the app (minus daily sampling) and guidance on how to use the content. An initial follow-up period of 1 month has been chosen for ethical purposes to minimize the amount of time control participants will wait before receiving the app. For participants in the intervention groups, the study aims to conduct an additional evaluation of outcomes 3 months following the intervention. A graphical summary of the study design is presented in Figure 1.

**Figure 1 figure1:**
[figure not shown]
Graphical representation of the randomized controlled trial protocol. CBT: cognitive behavioral therapy; RNT: repetitive negative thinking.

Participants will be randomly assigned, using a random-number generator, to 1 of 4 conditions: (1) intervention condition (therapist support); (2) intervention condition (no therapist support); (3) partial intervention (daily sampling and emotion valuation questions); or (4) control group (only daily sampling questions). Active control groups will be utilized to avoid artificially inflating comparisons with intervention condition outcomes [64]. The specific group allocations and the nature of other study conditions will be concealed from participants. Block/random stratification will not be used, as participants will be randomly allocated to 1 of the groups after agreeing to participate in the study. During analysis, demographic characteristics across groups will be compared, and any significant differences identified will be included as control variables.

Therapist support has been shown to improve outcomes in studies of digital mental health interventions [61]. In this study, therapist support will take the form of asynchronous written communication with a cognitive behavioral therapy (CBT) practitioner—either fully qualified or in at least their second year of training—via WhatsApp (Meta Platforms, Inc). This support will be available 2 times a week to relevant participants at specific times predetermined by the therapist. Participants will have the option to utilize this support, but will not be directed to do so. Supporting therapists will be paid at their standard hourly rate for regular patients and will receive an introduction to the app and intervention—while remaining blinded to the full aims of the study—through an online workshop conducted by members of the research team experienced in delivering rumination-focused cognitive behavioral therapy (RFCBT), before the study.

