### Participants and Power Analysis

Participants who self-report problems with RNT will be sought. The first participation in the trial is planned to commence in May 2025. As the study will be conducted remotely and recruitment will continue beyond this date, participants are expected to begin their engagement asynchronously.

To be eligible for the trial, participants must self-report problems with RNT. Participants will be excluded if (1) they are under 18 years of age at the start of the trial; (2) they are currently receiving any form of psychotherapy; or (3) they are currently receiving any form of psychiatric medication. Participants with a psychiatric diagnosis will not be excluded, provided they meet the inclusion criterion and do not meet any of the exclusion criteria listed above.

Sample size was calculated using G*Power version 3.1 [65] for a repeated-measures design with 4 independent conditions measured at 3 time points and assuming a medium effect size. This indicated a required sample size of 60 with equal randomization of participants across groups, which aligns with previous intervention studies in the field [66-68]. As our initial feasibility study during the development of the app content experienced an attrition rate of approximately 60% [69], this study aims to recruit at least double that number to mitigate the risk of significant dropout throughout the trial.

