### Recruitment Strategy

Participants will be recruited through online advertising on social media platforms (Facebook/Instagram; Meta Platforms, Inc) and via the laboratory website, where a contact email address will be provided for interested individuals to express their interest in participating. Full study information will be sent by email to all interested participants, and informed consent will be obtained via email response before the delivery of the app and the commencement of participation. To minimize information sharing across groups, participants will not have access to one another’s contact or identity details. Additionally, the current version of the app does not allow users to contact other participants or to determine how many others are using the app.

Recruitment is expected to begin in early May 2025 and will continue until the target number of participants in each condition has been reached. Participants may withdraw from the study at any time by contacting the research team via a designated email address provided in the study information form or through a link within the app. All data associated with participants who choose to withdraw will be fully removed from the study and destroyed. Participants will receive financial compensation of €50 (US $56) for taking part in the study.

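### Simple randomisation without blocks fits poorly with the equal arms behind the sample size and with recruiting until every condition is full, and the reason given for not blocking is not one

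*Protocol article*

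**What the plan says.** Study Design fixes the allocation method: "Participants will be randomly assigned, using a random-number generator, to 1 of 4 conditions". It then rules out restriction: "Block/random stratification will not be used, as participants will be randomly allocated to 1 of the groups after agreeing to participate". No other balancing method is described. Demographic differences between groups are to be compared at analysis, and significant ones used as control variables.

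Participants and Power Analysis gives a "required sample size of 60 with equal randomization of participants across groups", calculated "for a repeated-measures design with 4 independent conditions measured at 3 time points and assuming a medium effect size". Because the pilot lost about 60% of its participants, "this study aims to recruit at least double that number to mitigate the risk of significant dropout throughout the trial".

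Recruitment Strategy says that recruitment "will continue until the target number of participants in each condition has been reached". The Abstract and the Results section repeat a per-condition end point for data collection. The per-condition number is never written. Four equal arms imply 15 each from 60, or 30 each from 120.

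**The concern.** A random-number generator without restriction gives each person an equal chance of each arm, but does not give a set number per arm. Combined with a rule that waits for every arm to fill, it leaves three routes, and the article does not say which applies:

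- Keep all four arms open until the slowest fills. The others overshoot and total enrolment exceeds four times the target.
- Close each arm as it fills. Allocation probabilities then change during the trial, arm becomes linked to calendar time, and anyone who knows the counts can predict the last assignments.
- Stop at a fixed total. The arms are then unequal and the stated stop rule is not met.

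The choice would fall to the team in mid-recruitment. Over-enrolment has a cost: each participant is paid €50, one arm uses paid therapist time, and enrolment is planned for May to July 2025.

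**Working it through.** **Reproducing the plan's 60.** The article names G*Power 3.1, four groups, three time points and a medium effect. It does not give alpha, power, the correlation between time points or the F test used. I assumed f = 0.25, alpha 0.05, correlation 0.5, sphericity and the group-by-time interaction:

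- λ = f²·N·m/(1−ρ) = 0.0625 × 60 × 3 / 0.5 = 22.5
- df1 = (4−1)(3−1) = 6; df2 = (60−4)(3−1) = 112
- Power = 0.954, and 60 is the smallest multiple of 4 that reaches 0.95.

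So 60 is reproducible with equal arms. The match is not unique: correlation 0.4 with 90% power also gives 60, and other settings give from about 20 to over 200.

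**Arm sizes and totals under simple randomisation.** The probability of exactly equal arms is N! / [((N/4)!)⁴ · 4^N]. The remaining rows come from simulation with probability 0.25 per arm: 400,000 draws for arm sizes, 40,000 for filling every arm, and 20,000 for closing arms as they fill.

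| Quantity | 60 (15 per arm) | 120 (30 per arm) |
|---|---|---|
| Exactly equal arms | 0.2% | 0.08% |
| Smallest arm, mean (5th–95th percentile) | 11.1 (8–14) | 24.5 (20–28) |
| Largest arm, mean (5th–95th percentile) | 19.1 (16–23) | 35.7 (32–41) |
| Largest at least 1.5 times smallest | 72% | 42% |
| Total to fill every arm, all kept open: mean (median; 95th percentile) | 76.6 (75; 95) | 143.3 (141; 167) |
| If arms close when full: allocations after first closure, mean | 15 | 22 |
| If arms close when full: fully determined last allocations, mean (95th percentile) | 3.1 (7) | 4.3 (10) |
| Harmonic-mean arm size relative to nominal: mean (5th percentile) | 95% (86%) | 97% (93%) |

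One given arm fills after 15/0.25 = 60 or 30/0.25 = 120 people on average. The stop rule waits for the slowest of four, which adds the excess: 76.6/60 = 1.28 and 143.3/120 = 1.19, or 28% and 19% extra. At 30 per arm that is about 23 people, or 23 × €50 = €1,150 in participant payments, plus therapist time for those in the supported arm.

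**Cost in precision.** At the 5th percentile for 60 randomised, effective N is 0.86 × 60 ≈ 52, where power is still about 0.90 under the assumed inputs. For a single two-arm contrast with an illustrative standardised difference of 0.8 (two-sided 5%), power is 0.59 with 15 v 15 and 0.56 with 11 v 19. It is 0.87 with 30 v 30 and 0.86 with 24 v 36.

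**With permuted blocks.** Whole blocks in multiples of 4 give exactly 15 per arm at 60 and 30 per arm at 120. Every arm then reaches its target at the planned total and none closes early.

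**The case against.** Simple randomisation is valid, and several stronger readings that a reader might infer are not supported.

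- *The methods and sample-size sections contradict each other.* Equal randomisation can mean equal probability, which an unrestricted generator provides. What remains is a poor fit with the equal arm sizes that the calculation implies.
- *Arms of 11 and 19 are to be expected.* Those figures are for 60 randomised. The plan is to recruit at least 120, where imbalance is proportionally smaller.
- *Needing 143 breaches a stated total.* The plan says at least double, so 120 is a floor. The excess costs time and money but breaks no stated limit.
- *Concealment will be broken.* Nowhere does the article say that full arms will be closed. If all stay open, every allocation remains random. Even with closure, most later allocations are still random among the open arms, and only about the last 3 or 4 are fixed on average.
- *The trial loses its power through imbalance.* The calculations above show a small loss.

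Two ambiguities also count for the plan. The phrase on blocks and stratification is loose and may reject only stratification by covariates. And the target might mean completers. In that case 77 and 143 do not apply, and blocking alone would not equalise completers under attrition of about 60%.

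These points narrow the concern but do not remove it. The reason given does not bear on blocking under any reading, and the article fixes a per-condition stop rule beside an allocation method that cannot deliver it without overshoot or intervention. An article may leave operational detail to a fuller document; here, though, the statements it does make need reconciling.

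**Conclusion.** The concern holds in limited form. The rationale for not blocking is mistaken, and unrestricted allocation fits poorly with the implied equal arms and the per-condition stop rule. Followed as written with all arms open, the plan over-enrols by about 19% on average at 30 per arm, or 28% at 15 per arm. If filled arms were closed, about 22 of 120 allocations (15 of 60) would have altered probabilities, and the last few would be determined.

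These figures assume allocation probability 0.25 throughout, per-arm targets of 15 or 30 inferred from the totals, and a target that counts randomised participants. The power figures also rest on G*Power inputs that the article does not state. The issue does not invalidate the trial or its sample size. It is worth correcting before arms begin to fill, for allocation integrity, balance and economy of recruitment.

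**What to change.** In Study Design, replace the no-blocking sentence with a computer-generated list of permuted blocks of randomly varying size in multiples of 4 (for example 4 and 8), concealed from whoever enrols participants. In the Abstract, Recruitment Strategy and Results, replace the per-condition stop rule with a fixed total randomised, for example 120, and build the list so that whole blocks sum to it. State that the total counts randomised participants. Whether 120 is enough after dropout is a separate question that this change does not settle.

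If simple randomisation is kept, define the per-condition target, say what happens when one arm fills first, and remove the present rationale.

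The cost is only the work of generating and concealing the list. Enrolment is remote and individual, so nothing else in the conduct of the trial need change.
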